#### Effectiveness analysis on primary and secondary outcome measures

To examine differences between the two conditions on all outcome measures, analysis of variance for repeated measures (group x time) will be used. If demographic or outcome measures differ significantly between the groups at baseline, these measures will be incorporated into the analysis as covariate(s). Planned polynomial contrasts are used to analyze differences in effect of the program post-intervention and after the follow-up in the experimental group. Effect sizes of the experimental group in primary and secondary outcomes at post-intervention and follow-up will be calculated with Cohen’s D using the means and pooled standard deviations of the measurements of the conditions. Effect sizes are considered according to Cohen [79] as follows: small d=0.2, medium d=0.5, and large d=0.8. To see if subgroups (e.g., high/low age, gender, disease severity) respond better to the program, subgroup analyzes will be calculated using independent t-tests or Mann–Whitney tests.

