## Methods and design

### Participants

The study has been approved by the medical ethics committee Twente, number NL40257.044.12. Participants are recruited via arthritis clinics in four general hospitals in The Netherlands, located in the East and Southeast areas of the country. Moreover, people from existing databases of research participants are invited to participate. Also local newspapers and contacts with patient organizations are used to reach potential participants. The process for obtaining participant informed consent is in accordance with all applicable regulatory requirements.

The research population consists of people with polyarthritis (as defined by the DBC classification system) with a psychological risk profile. The specific inclusion criteria are: 1) age of 18 years or over, 2) diagnosis of polyarthritis, and 3) score of four or higher on the depression subscale of the Hospital Anxiety and Depression Scale (HADS). People with severe distress are excluded and the treating rheumatologist is informed. Severe distress is measured as a total score on the HADS (the total of both the depression and anxiety subscales) of 22 or higher. The cut-off score is based on literature [59,60]. In addition, insufficient Dutch language skills and actual enrolment in psychotherapeutic treatment at the moment of study are exclusion criteria.

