### Measurements

Table 3 gives an overview of the properties of the measurement instruments used. Participants are asked to complete six questionnaires including: intake, baseline (T0), directly after the end of the program (T1), 2 months after the end of the program (T2), 4 months after the end of the program (T3), and 6 months after the end of the program (T4). Nearly all the instruments listed in Table 3 were applied in a previous study with polyarthritis patients [12], and, when available, Cronbach’s alphas from that previous study also appear in Table 3.

**Table 3 T3:** Study parameters, properties of the corresponding instruments and their measurement point(s)

**Content**	**Measurement point**	**Scale**	**Reference**	**Example item**	**Scale range**	**Cronbach’s alpha **^**a**^	**Items**	**Response options**
Depression	Intake, T0, T1, T4	Hospital Anxiety and Depression Scale (HADS)	Zigmond & Snaith, 1983 [60]	I have lost interest in my appearance.	0-21	.81	7	various response format (0–3)
Anxiety	Intake, T0, T1, T4	HADS	Zigmond & Snaith, 1983	I feel tense or wound up.	0-21	.83	7	various response format (0–3)
Positive affect	T0, T1, T4	Positive subscale of the Positive and Negative Affect Schedule (PANAS)	Watson, Clark, & Tellegen, 1988 [67]	Rate how you felt during the past week: e.g., *attentive*, *interested*.	10-50	.92	10	very slightly or not at all (1) - very much (5)
Purpose in life	T0, T1, T4	Purpose In Life scale (PIL)	Ryff, 1989 [68]; Ryff & Keyes, 1995 [69]	My daily activities often seem trivial and unimportant to me.	6-30	.82	6	strongly disagree (1) -strongly agree (5)
Social participation	T0, T1, T4	Family role, autonomy outdoors, social relations and work and education subscales of the Impact on Participation and Autonomy (IPA) questionnaire	Cardol, De Haan, De Jong, Van den Bos, & De Groot, 2001 [70]	Domain autonomy outdoors: The possibility to spend my (spare) time like I want to is…	0-4	.76	25	very good (0) - very poor (4)
Pain	T0, T1, T4	1 item with 100 mm visual analogue scale	-	Please indicate how much pain you had in the last 7 days due to your condition?	0-100	-	1	no pain at all (0) -unbearable pain (100)
Fatigue	T0, T1, T4	1 item with 100 mm visual analogue scale	-	Please indicate your level of fatigue averaged over the past 7 days?	0-100	-	1	no fatigue (0) -completely exhausted (100)

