### Sample size

The sample size calculation is based on depressive symptoms as a primary objective. In order to demonstrate a medium-sized effect (Cohen’s *d* = 0.40), 100 participants in each condition are required, based on a statistical power (1-beta) of 0.80, a two-sided test and an alpha of 0.05 (power calculation with G-power).

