### Analysis

#### Preliminary analysis

A flow chart of participation during the total study will be drawn. Reasons for dropout will be summarized. Percentages of missing values and dropout will be displayed. Background variables and summarized scores on questionnaires will be given. One-way ANOVA’S and *χ*^2^-tests will be performed to check for differences between the two conditions at baseline for any of the demographic variables and/or outcome measures. Intention to treat-analyzes will be conducted with use of baseline (T0) or post-intervention (T1) data depending on the last present measurement data.

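### HADS depression and anxiety are scored twice before the programme, but the planned analysis gives the intake score no role and adjusts for T0 only after a significant baseline test, which loses precision without causing bias

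*Protocol article*

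**What the plan says.** The Measurements section keeps intake and baseline apart: "Participants are asked to complete six questionnaires including: intake, baseline (T0), directly after the end of the program (T1"), followed by three later follow-ups. In Table 3 the rows for HADS depression and HADS anxiety read "Intake, T0, T1, T4". No other outcome has an intake score.

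The Participants section uses the HADS for entry. The lower limit is a "score of four or higher on the depression subscale of the Hospital Anxiety and Depression Scale (HADS"). The upper limit is an exclusion: "Severe distress is measured as a total score on the HADS (the total of both the depression and anxiety subscales) of 22 or higher". Every enrolled participant should therefore have an intake score.

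The section on effectiveness analysis fixes one model for every outcome: "analysis of variance for repeated measures (group x time) will be used". Its covariate rule is conditional: "If demographic or outcome measures differ significantly between the groups at baseline, these measures will be incorporated into the analysis as covariate(s"). The intention-to-treat rule under Preliminary analysis names T0 as the only pre-programme score: "with use of baseline (T0) or post-intervention (T1) data depending on the last present measurement data". The mediation analysis also works from baseline and post-intervention scores. None of these sections mentions intake.

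**The concern.** A group x time test in a two-arm trial rests on change from the pre-treatment score. Change carries the variability of T0 in full. A covariate-adjusted comparison weights T0 by how well it predicts the outcome, and its residual variance is never larger than the variance of change. The plan allows that adjustment only when a baseline test happens to be significant, which in a randomised trial is a chance event unrelated to how prognostic the score is.

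A second pre-programme score on the primary outcome is also available for everyone, and the stated analysis does not use it. The Sample size section powers the trial at 0.80 and states no allowance for dropout, so precision on the primary outcome is worth having when the data are collected anyway.

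**Working it through.** **The plan's own figure.** The Sample size section gives d = 0.40, two-sided alpha 0.05 and power 0.80. The normal approximation is n = 2(1.960 + 0.842)²/0.40² = 98.1, so 99 per arm; the t-test gives 100, with power 0.804. The stated 100 reproduces. It is a plain two-group calculation that relies on no baseline score.

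**Inputs for the comparison.** The documents give no SD, mean or between-occasion correlation for the intake score. Assumed: unselected intake mean 5, SD 3.5, normal, selected at 4 or higher. The upper exclusion is ignored, and one follow-up (call it T1) is compared at a time.

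**Selection.** With a = (4 − 5)/3.5 = −0.286 and λ = φ(a)/(1 − Φ(a)) = 0.625, the intake variance shrinks by the factor k = 1 + aλ − λ² = 0.430. For occasions i and j, after selection on intake I, in units of the unselected variance:

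Cov(i, j) = r(i,j) − (1 − k)·r(I,i)·r(I,j).

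**Worked case, all correlations 0.6.**
- Var(T0) = Var(T1) = 1 − 0.570 × 0.36 = 0.795.
- Cov(T0,T1) = 0.6 − 0.570 × 0.36 = 0.395.
- Change from T0: 2(0.795 − 0.395) = 0.800.
- T0 as covariate: 0.795 − 0.395²/0.795 = 0.599.
- T0 and intake as covariates: 1 − 2(0.36)/1.6 = 0.550. Conditioning on intake removes the effect of selection.
- Both covariates against change: 1 − 0.550/0.800 = 31%. Intake beyond T0: 1 − 0.550/0.599 = 8%.

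**Other patterns.** Correlations are listed as intake–T0 / intake–T1 / T0–T1.

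| Correlations | Change from T0 | T0 covariate | T0 + intake | Both v. change | Intake beyond T0 | Change from mean of intake and T0 (v. change from T0) |
|---|---|---|---|---|---|---|
| .60/.60/.60 | 0.800 | 0.599 | 0.550 | −31.2% | −8.1% | 0.577 (−27.8%) |
| .70/.70/.70 | 0.600 | 0.475 | 0.424 | −29.4% | −10.9% | 0.437 (−27.1%) |
| .80/.80/.80 | 0.400 | 0.337 | 0.289 | −27.8% | −14.3% | 0.294 (−26.4%) |
| .75/.60/.65 | 0.687 | 0.567 | 0.549 | −20.2% | −3.2% | 0.582 (−15.3%) |
| .65/.50/.75 | 0.487 | 0.437 | 0.437 | −10.3% | 0.0% | 0.515 (+5.7%) |
| .70/.60/.80 | 0.394 | 0.359 | 0.357 | −9.5% | −0.5% | 0.414 (+5.1%) |
| .80/.64/.80 | 0.385 | 0.360 | 0.360 | −6.6% | 0.0% | 0.421 (+9.4%) |

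The first three rows have equal correlations; in the other four they decay with time. The two-covariate model is never worse than T0 alone. Averaging intake with T0 helps in some rows and harms in others.

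**Regression to the mean.** With all correlations 0.7, mean intake after selection is 5 + 3.5 × 0.625 = 7.19, and mean T0 is 5 + 0.7 × 3.5 × 0.625 = 6.53. Averaging the two would raise the pre-treatment level by (7.19 − 6.53)/2 = 0.33 points with no treatment involved.

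**The case against.** The strongest reply is that nothing here is an error. The sample size reproduces, the arm comparison is unbiased, and a second pre-treatment covariate is a refinement. That stands. A reader might infer from the unused score that the trial is biased or undersized. The documents do not support this: both arms are selected by the same intake rule, and the calculation behind "In order to demonstrate a medium-sized effect" needs no baseline score.

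A reader might also infer that the intake score is deliberately discarded. The article is silent; it neither lists the time points in the ANOVA nor excludes intake, and a fuller document might use it. What the article does fix is the model and the conditional covariate rule, and under these T0 is not routinely adjusted for and intake has no part.

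The third objection is that the gain from intake may be close to nothing. That stands too. Intake is the earlier score, recruitment draws partly on existing research databases, and groups of 8 to 10 must be formed, so a long interval and decaying correlations are plausible.

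Two further readings go too far. One is that averaging intake and T0 is a free gain. It can raise the variance by 5 to 9%, and its upward shift, which cancels between arms, would not cancel in the polynomial contrasts planned within the experimental group. The other is that the alpha of .81 in Table 3 measures error between occasions. It measures internal consistency and says nothing about stability over time.

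**Conclusion.** The point holds as a loss of efficiency. In the patterns examined, pre-specifying T0 and intake as covariates gives about 7 to 31% less variance than a change from T0. Most of the assured part comes from adjusting for T0 whatever the baseline test shows: T0 alone gives 6.6% in the least favourable row and 25% in the 0.6 row (1 − 0.599/0.800). Intake adds 8 to 14% beyond T0 under equal correlations and about 0 to 3% under decay.

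These figures rest on assumed correlations, an assumed intake distribution, one follow-up at a time, and no upper exclusion. They also assume that both scores precede allocation. Intake should, since it decides eligibility. The article does not state the order of T0 and randomisation.

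**What to change.** For HADS depression and HADS anxiety, state in the effectiveness analysis that the between-arm comparison at T1 and at T4 includes the T0 score and the intake score as separate covariates, whatever the baseline tests show. Do not average intake with T0, and do not enter intake as a level of the time factor: it is selected at 4 or higher, so a fall to T0 is expected in both arms without treatment. The other outcomes have no intake score and are not affected by that part of the change.

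The cost is one line of wording and one degree of freedom per added covariate, out of about 198 (2 × 100 − 2). The data are already collected, and the sample size need not change.

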**Methods/design:**

The protocol-based psycho-educational program consists of six group-based meetings and homework assignments, led by a trained nurse. Participants are introduced to goal management strategies and learn to use these strategies to cope with threatened personal goals. Four general hospitals participate in a randomized controlled trial with one intervention group and a waiting list control condition.

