### Randomization

The participants are assigned in a 1:1 ratio to either the experimental group or the control group. Patient allocation is be done by means of blocked stratified randomisation per site in random block sizes of 2 and 4 to make sure that both conditions are equally distributed in each participating hospital. The study is open label, as it is impossible, due to the nature of the program, to blind the staff and participants involved to the condition which the patient is allocated.

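### Baseline significance tests decide which covariates enter the primary model, so chance fixes the model and the T0 score is used less efficiently than a prespecified adjustment would use it

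*Protocol article*

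**What the plan says.** Under Preliminary analysis, one-way ANOVAs and chi-square tests are planned "to check for differences between the two conditions at baseline for any of the demographic variables and/or outcome measures". The next section, Effectiveness analysis on primary and secondary outcome measures, specifies a repeated-measures ANOVA with a group-by-time term for every outcome and adds the covariate rule: "If demographic or outcome measures differ significantly between the groups at baseline, these measures will be incorporated into the analysis as covariate(s". No covariate is fixed in advance.

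Table 3 schedules the HADS depression score at intake, T0, T1 and T4, so T0 is one of the repeated measurements.

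Randomization describes 1:1 allocation by "blocked stratified randomisation per site in random block sizes of 2 and 4". Sample size states that "100 participants in each condition are required, based on a statistical power (1-beta) of 0.80, a two-sided test and an alpha of 0.05", for d = 0.40. No gain from covariates is assumed there.

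**The concern.** A significance test of a baseline difference between randomised arms tests a hypothesis that is true by design. A positive result shows chance imbalance. It does not show that the variable predicts outcome. The rule therefore chooses covariates for the wrong reason, and three things follow.

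- **The primary model is not fixed.** Which model tests the main hypothesis depends on a set of baseline p-values.
- **The T0 score can have two roles.** The rule covers outcome measures explicitly. If T0 depression differs, it becomes a covariate in a model that also has T0 depression as its first repeated outcome. A group-by-time test that includes T0 and a comparison adjusted for T0 are different analyses, and chance would decide between them.
- **Precision is left unused.** The T0 value of an outcome is usually a strong predictor of its later values. Always adjusting for it is at least as efficient as comparing changes from it, and the data are already collected.

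**Working it through.** **1. The plan's own figure.** Inputs from Sample size: d = 0.40, two-sided alpha 0.05, power 0.80. The two-sample t-test needs 99.08 per arm, which rounds up to 100; at 100 per arm its power is 0.804. The stated figure reproduces as an unadjusted comparison of two means.

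**2. How often the rule fires.** Demographics lists five variables. The abstract names eight outcomes (one primary, seven secondary), counting social participation once. That makes 13 tests. The article gives no level for them, so 0.05 is assumed.

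- At least one covariate enters, if the tests are independent: 1 − 0.95^13 = 0.487.
- Several scales are related (depression with anxiety, pain with fatigue and function), so the true figure is lower.
- For T0 depression alone the chance is 5%.

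A demographic variable that does not change over time alters a group-by-time test only if it predicts change.

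**3. What the T0 score contributes.** For T0 to T1, the group-by-time term compares mean changes between arms. Let rho be the correlation between T0 and T1 scores and take the score variance as 1.

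- Change comparison: variance factor 2(1 − rho).
- T1 adjusted for T0: variance factor 1 − rho².
- Noncentrality of the t-test: (0.40/√factor) × √(100/2).

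At rho = 0.5 the change factor is 1.00, giving 0.40 × 7.07 = 2.83 and power 0.80. The adjusted factor is 0.75, giving 0.462 × 7.07 = 3.27 and power 0.90.

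**4. Power under the stated rule.** I simulated the rule with 100 per arm, d = 0.40 and 40,000 replicates. The change comparison is used unless T0 differs at p < 0.05, in which case T0 is adjusted for. For this contrast, regressing the change on arm and T0 gives the same arm effect as regressing T1 on arm and T0. The article gives no rho, so a range is shown.

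| Assumed rho | Change comparison only | Stated rule | T0 always adjusted for | Gain over the rule (points) |
|---|---|---|---|---|
| 0.3 | 66% | 68% | 84% | 16 |
| 0.4 | 73% | 74% | 87% | 13 |
| 0.5 | 80% | 81% | 90% | 9 |
| 0.6 | 88% | 89% | 94% | 5 |
| 0.7 | 95% | 96% | 98% | 2 |

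The group-by-time F test over T0, T1 and T4, with equal effects at T1 and T4 and no covariate, gives a similar picture: 70%, 83% and 97% at rho 0.3, 0.5 and 0.7 (4,000 replicates).

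**5. Type I error of the rule.** With no treatment effect, the same simulation rejects in 3.9%, 4.1%, 4.1%, 4.5% and 4.6% of replicates at rho 0.3 to 0.7. All are below the nominal 5%.

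**6. Hospital.** For a single post-treatment score, with hospital assumed to explain 1% to 10% of the variance, adding hospital raises power from 0.809 to 0.811 at the low end and from 0.820 to 0.846 at the high end. That is a gain of 0.2 to 2.6 points. For the group-by-time term the gain is about nil if hospitals differ only in level, since level differences cancel within a person.

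**The case against.** The strongest reply is that the plan already uses baseline. T0 is a level of the time factor, so every analysis works with change from T0 whether or not the rule fires. A reader might infer that baseline depression is ignored in all but about 5% of trials, or that power already paid for is thrown away. Neither follows. What is lost is efficiency relative to adjustment for T0, and the loss shrinks to about 2 points at rho = 0.7.

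A second reply is that the sample size claims no covariate gain and reproduces. That stands: the 100 per arm is not shown to be wrong. The change comparison falls short of the planned 80% only if rho is below about 0.5, and the article does not give rho.

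Third, a reader might infer that choosing covariates from the data inflates false positives. The check shows the opposite for this rule: it is slightly conservative.

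Fourth, a reader might count the absence of a hospital term as an error, since allocation is stratified by hospital. The article neither includes nor excludes one, and a condensed article can leave that to the full protocol or analysis plan. The effect on power is also small.

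None of these replies reaches the covariate rule itself. It is stated outright, and an analysis plan that followed the article would carry it over.

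**Conclusion.** The point holds in a limited form. Baseline significance tests select the covariates, so the primary model is settled only after the data are seen. The chance that at least one of 13 variables enters is up to about 49%, assuming independent tests at 0.05. A T0 outcome that differs by chance would stand on both sides of the model.

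The cost is precision and a model that is not fixed; validity is not threatened. For T0 to T1 with 100 per arm and d = 0.40, always adjusting for T0 gains about 16 points of power at rho = 0.3, 9 at 0.5 and 2 at 0.7. These figures rest on assumed correlations, equal variances, normal scores and no dropout.

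**What to change.** Delete the rule that makes a baseline p-value the condition for adjustment, together with the tests that feed it, and report baseline characteristics by arm descriptively. For each outcome, prespecify a comparison of the arms at T1 and T4 adjusted for the T0 value of that outcome, with T0 not also an outcome level. A longitudinal model that includes T0 with a common baseline mean for the two arms is an equivalent choice. Name any further covariates in advance, on prognostic grounds.

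Hospital, as the stratification factor, can be added as a fixed term. This is a minor addition with little effect on power.

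The cost is a slight rewording of two analysis sections. The T0 values are already scheduled and hospital is known from randomisation, so no extra participants, visits or measurements are needed.

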### Demographics and disease related measures

#### Demographics

Baseline measurement includes demographic variables, including sex, age, marital status, education and current state of employment.

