### Strengths and limitations of the randomized controlled trial

Our study will hopefully answer questions regarding the effectiveness of the goal management intervention for patients with a rheumatic disease. We try to understand the pathways that are responsible for successful adaptation in persons dealing with a rheumatic disease and investigate who benefits most. In addition, we have included an economic evaluation. However, these additional analyzes cannot be conducted in absence of an effect of the goal management intervention compared to the waiting list group.

As the “Right On Target” program is a newly developed intervention, we execute a stakeholders’ analysis. Experiences of participants, trainers and the management of the participating clinics provides insight into the feasibility regarding the intervention. The information from the stakeholders’ analysis supports future implementation of the intervention.

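### Splitting age into high and low groups, with no stated cut, wastes information on who benefits if benefit changes smoothly with age

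*Protocol article*

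**What the plan says.** In the protocol article, the section on effectiveness analysis of primary and secondary outcomes introduces the subgroup work with "To see if subgroups (e.g., high/low age, gender, disease severity) respond better to the program" and gives the method as "subgroup analyzes will be calculated using independent t-tests or Mann–Whitney tests". High/low age stands in a parenthesis of examples. No cut-point is given there or elsewhere, and no clinical reason for one.

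Age is a baseline item: "Baseline measurement includes demographic variables, including sex, age, marital status, education and current state of employment". The Participants section admits anyone with "age of 18 years or over", so the possible range is wide.

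The Discussion, under strengths and limitations of the trial, lists among the study's purposes to "investigate who benefits most". The subgroup sentence is the analysis that serves this purpose. The Sample size section is built on the primary outcome alone: "100 participants in each condition are required", for an effect of d = 0.40.

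**The concern.** A high/low split treats two people just either side of the cut as different, and two people decades apart on the same side as the same. If the program's effect rises or falls gradually with age, the split throws away part of the evidence for that gradient. The result can also depend on where the cut falls.

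This is a question about the scale of the moderator. It would remain if the two-group tests were replaced by a formal treatment-by-subgroup interaction but age stayed in two groups. What is at stake is the answer to who benefits most: a trial sized only for the main effect has limited power for any moderator, and a real age gradient becomes more likely to be reported as absent.

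**Working it through.** **The plan's own figure.** Inputs from Sample size: d = 0.40, power 0.80, two-sided alpha 0.05. The normal approximation gives n = 2 × (1.960 + 0.842)² / 0.40² = 98.1, so 99 per arm. With the exact noncentral t, power is 0.7997 at 99 and 0.8036 at 100. The stated 100 per arm reproduces, giving N = 200 at 1:1 allocation.

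**Information kept by a split.** For a linear gradient, the share kept is the squared correlation between age and the high/low indicator. For a symmetric distribution cut at the median, that correlation is the mean absolute deviation divided by the SD.

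- Normal age: (√(2/π))² = 2/π = 0.637, so 36% is lost.
- Uniform age on (−1, 1): (0.5 / √(1/3))² = 0.75, so 25% is lost.
- Mildly skewed age, median cut (simulated): 33% is lost.
- Normal age cut 30/70: 42% is lost. Cut 20/80: 51% is lost.

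**Power of an interaction test.** Let b be the change in program effect, in outcome SDs, per SD of age. With residual SD 1 and 1:1 allocation, the standard error of the interaction is 2/√N. The noncentrality is therefore nc = b√200 / 2 = 7.071b for continuous age. For the split it is nc × √(share kept), which is nc × 0.798 for normal age. Power is Φ(nc − 1.96) + Φ(−nc − 1.96).

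For b = 0.2, nc is 1.414 with continuous age and 1.128 with the split, giving power of 29.3% and 20.4%.

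| b (assumed) | continuous | median split, normal age | loss (points) | loss if age is uniform |
|---|---|---|---|---|
| 0.1 | 10.9% | 8.7% | 2.2 | 1.5 |
| 0.2 | 29.3% | 20.4% | 8.9 | 6.1 |
| 0.3 | 56.4% | 39.5% | 16.9 | 11.3 |
| 0.4 | 80.7% | 61.7% | 19.1 | 12.0 |

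Losses were taken before rounding. A simulation with normal age (4,000 runs per setting) gave losses of 8.8, 15.4 and 20.0 points at b = 0.2, 0.3 and 0.4, in agreement within simulation error. If only 160 were analysed, the loss at b = 0.2 would be 7.2 points.

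**When the split wins.** If the true effect is a step exactly at the median, with the program effect shifted by +0.3 SD on one side and −0.3 SD on the other, simulated power is 38% with continuous age and 51% with the split.

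**A comparison within the experimental arm only.** The plan does not say which two groups the t-test compares. If it compares high-age with low-age participants in the experimental arm (n = 100), nc = b√100 = 10b, with b now the slope in that arm. At b = 0.2, power is 51.6% with continuous age and 35.8% with the split, a loss of 15.8 points. The relative loss of information is the same.

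**The case against.** The strongest reply is that this is one example in a parenthesis, in a condensed article, for a secondary analysis. A cut-point is the kind of detail a fuller plan may hold, so its absence does not show that the cut will be chosen arbitrarily or after seeing the data. That stands. What the article does state, however, is the high/low form and tests that accept only two groups. Supplying a cut in another document would not restore the lost information.

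A reader might infer that the plan costs a third of the information and 9 to 19 points of power as a matter of fact. The documents do not support this. They give no age distribution, no cut and no expected gradient. At gradients of 0.1 and 0.15 the loss is 2.2 and 5.0 points. The largest figure comes from a gradient of 0.4, equal to the planned main effect. That would mean no benefit one SD of age to one side of the mean and double benefit one SD to the other. Nor is it stated that age is recorded in years: only the eligibility limit is expressed that way, and Table 3 gives the demographics a mixed response format. Recording in years is a reasonable inference only.

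It is also fair to say that the interaction test used in the power table is not one the plan names, and that age cannot be kept continuous without replacing the two-group test. Both are true. They mean that the remedy must change the test as well as the scale of age; they do not remove the loss.

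Finally, none of the stated hypotheses concerns moderation by age, and the Discussion says the additional analyses depend on the program first showing an effect. This limits the importance of the point.

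**Conclusion.** The point holds as a low-impact weakness. The plan examines whether benefit depends on age by a high/low split with no stated or justified cut. If benefit changes smoothly with age, a median split loses roughly 25% to 36% of the information across uniform to normal age, and more for an uneven cut of normal age. The loss of interaction power, about 2 points at a gradient of 0.1 rising to about 19 at 0.4, rests on normal age, a median cut, a linear interaction and analysis of all 200 planned participants. The gradients themselves are assumptions. With a true step at the cut the direction reverses, but the protocol gives no reason to expect one. A reader should not infer that the primary comparison is affected; it is not.

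**What to change.** For age and any other continuous moderator, replace the high/low split and the two-group test with a treatment-by-moderator term in the outcome model, keeping the moderator continuous. Report the estimated program effect with its 95% CI at chosen values, such as the 25th, 50th and 75th percentiles. Keep groups for categorical factors such as gender. A high/low table may stay as a descriptive display.

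The cost is a sentence or so in the analysis section and no new data, provided age is recorded as a number at baseline, which should be confirmed. The downside is an assumed linear trend, which can be checked with a quadratic or spline term.
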